### Quantitative Data Collection

Quantitative data collection will include five survey data points as outlined below.

All surveys will be developed using the REDCap (Research Electronic Data Capture; Vanderbilt University) software, a computer-assisted survey platform with built-in data encryption [44]. All surveys will be completed using dedicated study tablets, which means participants will not be required to use their internet data. In addition, we will use a data-free survey completion option. The survey links will also be sent to participants who wish to complete the surveys on their own devices. There will be no data costs for participants for completing the assessments. Participants will be reimbursed ZAR 50 (US $3) in airtime toward their time.

Household surveys include 2-time points of data collection, a pre- and posttest design, as described below.

#### Sampling

Households were chosen through a simple random sampling method, and eligible participants were enrolled as follows: a minimum of 800 adult men and women aged 18 years and older, with 400 designated for the pretest and 400 for the posttest. At least 100 households with index participants aged 18-34 years will be approached per community. Nonindex participants include other adults in the households who are aged 18-34, 35-49, and 50 years and older who will also be invited to complete surveys.

#### Pre- and Posttest Surveys

Using a random sample of households having youth participants (18-34 y) generated from the HDSS database, adults will be approached in their households to complete a 15-minute online pretest assessment survey (Multimedia Appendix 1) to measure: sociodemographics (age, gender, food security, and potential loss of income), knowledge of influenza vaccines and benefits, health beliefs, and sources of health information (social media, television, radio, friends, and family), and vaccine confidence [45]. The same households will be invited to participate in the posttest household survey (Multimedia Appendix 2). The posttest household survey will be conducted after the study campaign intervention.

Clinic survey data collection with vaccinees (Multimedia Appendix 3) and those who declined vaccination (Multimedia Appendix 4) are described below.

All adults (older than 18 years) who received an influenza vaccination will be approached; as such, numbers may vary as this depends on who elects to vaccinate. However, a total of at least 400 (n=100 per community) youth (aged 18-34 y) participants who go to the intervention clinics will be purposively approached to complete a postvaccination assessment. The study team will work closely with health care workers at public health clinics in the study communities. Health care workers will refer patients after having received the influenza vaccine, on-site at the clinics. These participants will be invited to complete a brief survey using the same measures as specified for the pretest survey. The data will be covered as part of the project expenses. There will be no data costs for participants to complete the assessments. Participants will be reimbursed ZAR 50 (US $3) in airtime toward their time.

Additional measures will assess motivations for influenza vaccines, where participants heard about this or other drives for the influenza vaccination, if participants had seen any online messaging driving them to get the influenza vaccine or been exposed to specific community engagement activities, and whether it had influenced their decision to vaccinate, and online impressions, for example, video views rates (dependent on final campaign strategy and media mix) and their impact on vaccinations in that region. The uptake of influenza vaccines will be tracked in the 4 clusters across the study period.

Clinic attendees who decline vaccination will also be approached to complete surveys. These participants will be aged 18 years and older. Health care workers will refer patients who were offered vaccination as part of their clinic attendance but who declined vaccination. Those participants who agree to participate will be invited to complete a brief survey to understand the reasons for declining vaccination. The survey measures will include: if and where participants heard about this drive for the influenza vaccination, if participants had seen any online messaging driving them to get the influenza vaccine or been exposed to specific community engagement activities, and whether it had influenced their decision to vaccinate.

As with all the surveys, the data costs will be covered as part of the project expenses. There will be no data costs to participants for completing the assessments. Participants will be reimbursed ZAR 50 (US $3) airtime toward their time.

#### Qualitative Evaluation

Additional FGDs (Multimedia Appendix 5), including 10-12 participants per FGD, will be conducted: 8 midway through the intervention (during vaccination season) and 8 post intervention. These FGDs will be mixed gender and will be stratified by age group (18-24, 25-34 y), and community (2 per cluster). Key informant interviews (KIIs; n=20; Multimedia Appendix 6) with key influencers including, religious leaders, traditional healers, and youth leaders, as well as other influencers that would be identified through community engagement and communications activities.

### Data Analysis

#### Qualitative Data Preparation and Analysis Plan

FGDs and KII recordings will be transcribed verbatim and translated into English for analysis. Transcripts will be analyzed using a framework analysis approach. Framework thematic analysis provides a highly systematic method of categorizing and organizing data according to key themes, concepts, and emergent categories in grids or matrices [46]. Coding will follow a combined approach, ie, both deductive based on our hypothesized themes and inductive (data-driven) to allow for emerging themes. Priori coding based on the interview guide questions will be used to generate an initial coding framework [47]. After developing the initial coding framework, 2 researchers will read through 2 transcripts independently and code them line by line, to identify patterns and themes in the data [47]. This will allow us to further refine the domains and categorize the codes into themes and subthemes. Codes will then be captured using Dedoose, a qualitative data analysis software, and each transcript will be coded in Dedoose by at least 2 researchers and assessed for consistency in the coding of the first 5 transcripts [48]. The research team will convene to review the initial codes and apply general categories that will make up the analytic framework. Any coding disagreements will be discussed until an agreement is reached. This will allow for the finalization of the codebook, which will then be applied to the remaining transcripts. Rigor will be ensured through peer debriefing, triangulation with quantitative data, and member-check presentations with key stakeholders [49].

#### Statistical Analysis Plan

We will use descriptive statistics to describe study variables including knowledge of influenza vaccines, experiences with influenza vaccines, stigma, and vaccine confidence. Reliability assessments using the Cronbach alpha test will be evaluated for scale measures. Scales with poor reliability scores will be calibrated using factor analysis. Data will be analyzed overall and stratified by community. Frequencies will be determined for categorical measures whereas means (SD) and medians (IQR) will be determined for continuous measures. Pairwise comparisons of categorical measures between communities will be evaluated by the chi-square or Fisher exact test as appropriate. Similarly, pairwise continuous measures will be analyzed by the 2-sample *t* test, if satisfying normality distribution conditions or the Wilcoxon Mann-Whitney test, if nonnormally distributed. Normality will be assessed by the Shapiro-Wilks method. Drivers of knowledge, stigma, and experiences of influenza vaccines will be determined by logistic regression for binary outcomes and linear regression for continuous outcomes. Multivariable analysis will be carried out to adjust for potential confounders. Model fit statistics will be assessed on all multivariable regression models to ensure the validity of the findings. Data analyses will be conducted using SAS Enterprise (Guide 7.15; SAS Institute) [50].

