## Results

As of May 2024, all data collection is complete, with data analyses and preparation of peer-reviewed publications in progress. The results will encompass qualitative analysis of factors influencing influenza vaccine uptake, a pretest-posttest evaluation of interventions, and campaign intervention methodology along with a longitudinal household investigation of changes in perceptions and attitudes toward influenza vaccination. The first results are expected to be submitted for publication by November 2024.

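### The named tests and regressions assume independent respondents, but the household survey enrols several adults per household and re-surveys the same households

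*Protocol article*

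**What the plan says.** All places are in the protocol article.

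- **Two waves, same households.** Quantitative Data Collection: "Household surveys include 2-time points of data collection, a pre- and posttest design". Pre- and Posttest Surveys: "The same households will be invited to participate in the posttest household survey". It does not say whether the same individuals answer both times.
- **Several adults per household.** Sampling (under Quantitative Data Collection): "Nonindex participants include other adults in the households who are aged 18-34, 35-49, and 50 years and older". No cap or expected number per household is given.
- **Size.** The same section sets "a minimum of 800 adult men and women aged 18 years and older, with 400 designated for the pretest and 400 for the posttest", and adds "At least 100 households with index participants aged 18-34 years will be approached per community".
- **Tests.** Statistical Analysis Plan assigns chi-square or Fisher tests to pairwise comparisons of categorical measures between communities. It continues: "Similarly, pairwise continuous measures will be analyzed by the 2-sample" t test, or the Wilcoxon Mann-Whitney test for non-normal data. Drivers of knowledge, stigma and experiences are to be found by logistic or linear regression, adjusted for confounders. No household term, cluster-robust variance, mixed model, GEE or paired test is named.
- **Promised output.** Results lists a pretest-posttest evaluation and "a longitudinal household investigation of changes in perceptions and attitudes toward influenza vaccination".

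**The concern.** Adults in one household share information sources, beliefs and campaign exposure, so their answers are likely to be correlated. Answers from one household before and after the campaign are likely to be correlated too. The methods named count each questionnaire as a separate piece of information.

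In a comparison between communities, ignoring this makes the standard error too small and produces too many false positives. The same applies to regression coefficients for community or anything else that household members share. Confounder adjustment and model-fit statistics, which the section does mention, do not correct for it.

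For change over time, the plan collects data that allow an efficient before-after comparison but names no method that uses the link between waves. If the two-sample tests were carried over, the standard error would be too large and power would be lost.

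**Working it through.** **1. The plan's own count.** 4 communities x 100 households = 400 per wave; x 2 waves = 800. This matches the stated minimum and corresponds to one index respondent per household. No alpha, power, effect size or SD is given, so there is no sample-size calculation to reproduce.

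**2. Respondents per household (m).** The nearest figure is Table 1: youth 5824 + 6801 + 6848 + 5648 = 25,121; households with youth 3478 + 4037 + 4072 + 3831 = 15,418; ratio 1.63. It counts residents, not respondents, and leaves out adults of 35 and over. Values of 2 and 3 are assumptions.

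**3. Between communities, one wave.** Design effect D = 1 + (m - 1) x ICC. True SE / nominal SE = sqrt(D). Actual two-sided error of a nominal 5% test = 2 x [1 - Phi(1.96 / sqrt(D))]. The intraclass correlation (ICC) is not in the article; 0.1-0.5 is assumed. Example: m = 1.63, ICC = 0.3 gives D = 1 + 0.63 x 0.3 = 1.189, sqrt(D) = 1.090, actual error 7.2%.

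| m | D (ICC 0.1 / 0.3 / 0.5) | True / nominal SE | Actual error |
|---|---|---|---|
| 1 | 1.00 / 1.00 / 1.00 | 1.00 | 5.0% |
| 1.63 | 1.06 / 1.19 / 1.32 | 1.03 / 1.09 / 1.15 | 5.7 / 7.2 / 8.7% |
| 2 | 1.10 / 1.30 / 1.50 | 1.05 / 1.14 / 1.22 | 6.2 / 8.6 / 11.0% |
| 3 | 1.20 / 1.60 / 2.00 | 1.10 / 1.26 / 1.41 | 7.4 / 12.1 / 16.6% |

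**4. Between communities, both waves pooled.** Let r be the correlation between one person's two answers, and let two members' answers in different waves correlate at 0.8 x ICC (both assumed). The variance factor is 1 + (m - 1) x ICC + r + (m - 1) x 0.8 x ICC. With r = 0.5, m = 1 gives 1.5 and an actual error of 11.0%; m = 2 gives 1.68-2.40 and 13-21% for ICC 0.1-0.5. Pooling therefore inflates the error even with one person per household, if that person answers twice.

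**5. Pre-post change with a two-sample test, same persons, one per household.** Nominal SE / true SE = 1 / sqrt(1 - r).

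- r = 0.3: 1 / sqrt(0.7) = 1.20, 20% too large; actual error 1.9%.
- r = 0.5: 1 / sqrt(0.5) = 1.41, 41% too large; actual error 0.6%.
- r = 0.7: 1 / sqrt(0.3) = 1.83, 83% too large; actual error 0.04%.

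For an assumed change of 0.2 SD, r = 0.5 and 100 pairs, power is 52% with a paired analysis and 22% with the two-sample test; with 400 pairs it is 98% and 89%. Household clustering offsets part of the excess: with m = 2, ICC 0.3 and r = 0.5, the variance factor is 1 + 0.3 - 0.5 - 0.24 = 0.56, so the SE is 1 / sqrt(0.56) = 1.34 times its true value.

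**6. Simulation check.** 4000 runs, 100 households per community, m = 2, ICC 0.3, r = 0.5, no true effect. Rejection at nominal 5% was 8.1% between communities in one wave, 17.5% with waves pooled, and 0.6% for pre-post by the two-sample test. The direction and size agree with the formulas.

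**The case against.** **A reader might infer that the standard errors are wrong in both directions throughout.** The article does not support that. The sentence on categorical measures places the pairwise tests between communities, and the t-test sentence follows on from it. For those comparisons the error goes one way only: too small. No two-sample test is assigned to pre-post change, so the too-large direction is conditional on someone using one there. Leaving the longitudinal method to a fuller plan would be normal in a condensed article, and its absence alone would not be a finding. What remains is that the methods actually named do not fit the sample actually described.

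**At the stated minimum there may be no clustering.** With one index youth per household analysed in one wave, D = 1 and the tests are sound on this point. The article does not say that index and nonindex adults enter the same test. Equally, it does not restrict any test to index participants, and its minimum sample is defined as adults of 18 and older. This objection sets the boundary of the point but does not remove it.

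**The same persons may not answer twice.** Only households are said to be re-invited. If another member responds, the relevant correlation is the one between members, and the 20-83% range need not apply. This stands.

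**The regressions are not described as ordinary.** The article does not say how variances are estimated, so a robust estimator is possible. None is named, and the section is otherwise specific down to the normality test.

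**The magnitude is assumed.** This also stands: ICC, respondents per household and r are all absent from the article. Any error in the pre-post direction would be conservative, costing power rather than producing false positives.

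**Conclusion.** The point holds in conditional form. Applied as named to household data with more than one adult per household, or with the two waves pooled, the between-community tests and regressions understate the standard error. In one wave, under an assumed ICC of 0.1-0.5, the nominal 5% test runs at about 6-9% at Table 1's 1.63 per household and 6-11% at two. The inflation is nil for one index youth per household in a single wave.

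For the promised pre-post change, no paired or longitudinal method is named. Using the two-sample tests there would make the standard error 20-83% too large at an assumed within-person correlation of 0.3-0.7, and only if the same persons respond. The direction of each error follows from the design; the sizes are illustrations, not estimates for this study.

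**What to change.** For the household survey data, amend the Statistical Analysis Plan section as follows.

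1. Keep the household ID in the analysis file, and a person ID wherever individuals can be linked across waves. State whether the same individuals were re-interviewed.
2. Replace the independent-sample tests and regressions with GEE with robust standard errors, or mixed models, clustered on household. Add a person-level effect for those seen twice.
3. Analyse pre-post change in the same framework with a wave-by-community term.
4. Use McNemar or the paired t test only for individuals confirmed to have answered at both waves.
5. State for each analysis whether it uses index youth only or all adults, and one wave or both.

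The cost is wording and routine programming in the planned SAS software; no new data are needed beyond the identifiers. Some between-community intervals become slightly wider. The change corrects standard errors only: it does not separate the effect of an intervention from the effect of the community in which it was delivered.

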### Bias Correction

While the study is designed to focus on four relatively distinct geographic areas, due to the nature of social media and health care–seeking behaviors in the broader community of Soweto, it is possible that members from the intervention communities may interact with those not receiving the intervention. While potential interaction cannot be prevented entirely, research questions for all participants will include questions about exposure to intervention components and other potentially similar national or localized campaigns. In addition, a phased delivery of the interventions to ensure the offline intervention is not biased by the online intervention should help mitigate this.

It is also possible that those exposed to the interventions may seek to be vaccinated in clinics that are not included in the study’s geographically defined target areas. An effort will be made to collaborate with the Department of Health to broadly understand influenza vaccinations during the campaign season, in broader Soweto and areas where residents typically seek health care. Vaccine and vaccination sentiments broadly in Soweto and South Africa will also be tracked during the course of the project for context and monitoring of potential risk.

### Ethical Considerations

All research procedures were approved by the University of the Witwatersrand Human Research Ethics Committee (Medical; M230254) and the local Department of Health. Participants will be reimbursed ZAR 50 (US $3) airtime for survey completion and ZAR 150 (US $8) for the FGDs and the KIIs. This study will be conducted in accordance with the World Medical Association Declaration of Helsinki’s ethical principles for research involving human subjects and will align with the guidelines of the Protection of Personal Information Act (POPIA) 4 of 2013. A copy of the information leaflet detailing the nature and processes involved in the study will be given to the participants. Written informed consent will be obtained from participants before participation, and audio recording of KIIs and FGDs. All information about participants will be confidential and protected, and data dissemination will not include any identifiable information.

## Results

As of May 2024, all data collection is complete, with data analyses and preparation of peer-reviewed publications in progress. The results will encompass qualitative analysis of factors influencing influenza vaccine uptake, a pretest-posttest evaluation of interventions, and campaign intervention methodology along with a longitudinal household investigation of changes in perceptions and attitudes toward influenza vaccination. The first results are expected to be submitted for publication by November 2024.

## Discussion

### Principal Findings

This study will provide critical insights for improving the effectiveness of influenza vaccination campaigns in South Africa. Leveraging micro- and nanoinfluencers on social media, and collaboration with community influencers has been proven to reach and motivate target groups with low vaccine uptake [51]. This study will provide valuable insights into the use of microinfluencers online and offline to reach economically marginalized communities to make positive health decisions where the personal risk perception from not doing so is low in the absence of any mandated reasons to do so. It will also provide an assessment of the differing impact of campaign approaches and the value of the amplification of voices into online social networks for health outcomes.

### Dissemination Plan

Knowledge dissemination will include clear research into action goals through community-based gatherings and activations, radio, and social media–driven activities to key audiences. A strongly connected dissemination platform will be developed by starting with key partners attending an initial study planning meeting, including collaborators, scientists, health policy makers, and representatives from local groups and CAB to recruitment sites. A dedicated website will promote the study and health awareness. A results dissemination group comprising youth CABs and stakeholders will develop knowledge dissemination material for sharing with study participants, stakeholders, and the wider community. Results will be disseminated through press releases, community meetings, social media, and the website. This will be accompanied by scientific presentations to academia, fellow practitioners, and policy makers, publications in open-access peer-reviewed journals, and national and international meetings. Results dissemination meetings will be convened for all study communities and the CAB.

### Conclusions

Enhancing perceptions of, bolstering confidence in, and fostering uptake of vaccination relies heavily on the efficacy of yearly influenza vaccination initiatives, personalized education tailored to specific contexts, active community involvement, consistent vaccine availability, and easily accessible, cost-free distribution channels at the local level.

## Appendix

Multimedia Appendix 1 Household pretest survey.

Multimedia Appendix 2 Household posttest survey.

Multimedia Appendix 3 Clinic (vaccinated) survey.

Multimedia Appendix 4 Clinic (unvaccinated) survey.

Multimedia Appendix 5 Semistructured interview guide for focus group discussions.

Multimedia Appendix 6 Semistructured interview guide for key informant interviews.

## Abbreviations

CAB: Community Advisory Board
FGD: focus group discussion
HDSS: Health and Demographic Surveillance System
KII: key informant interview
LMIC: low- and middle-income country
POPIA: Protection of Personal Information Act
REDCap: Research Electronic Data Capture
Soweto: South-Western Township
WHO: World Health Organization
